#### **Criteria for withdrawal**

- The participant can withdraw from the study at any time without further motivation and without any consequences for his/her future treatment.
- The participant will be withdrawn should they develop any condition or begin taking any compound that is part of the exclusion criteria.
- A participant can be withdrawn if he/she does not adhere to the procedures as specified in the protocol. No extra financial or treatment compensation is given to the participant in that case.
- If the participant experience serious adverse events, and there are reasons to think that the event is related to the study, he/she will be immediately withdrawn and prompt action will be taken to assist the participant as necessary.
- The study can be stopped at any time due to a lack of treatment effect, side effects or that the procedures of the protocol are not adhered to. In that case all participants as well as relevant authorities will be notified.

All participants that are withdrawn will continue their regular medication and their ordinary physician will be notified as appropriate.

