##### **Exclusion criteria**

- Diagnosed with diabetes mellitus according to the WHO criteria
- Anti-diabetic medication
- Active liver disease

- At screening or at any subsequent visit a level of aspartate aminotransferase (ASAT) or alanine aminotransferase (ALAT) of more than three times the upper limit of the normal range
- Gastrointestinal ailments which may interfere with the ability to adequately absorb sulforaphane
- At screening visit creatinine > 130 µmol/L
- Coagulation disorder or current anti-coagulant therapy, which may be affected by the BSE
- Diagnosed with a cardiovascular disease or known cardiovascular event, transient ischemic attack, coronary by-pass surgery or other coronary vessel intervention within 6 months prior to enrolment
- Systemic glucocorticoid treatment
- Herbal treatment, defined as food supplement (except multivitamin treatment) with herbal or vegetable extracts that may affect blood glucose
- Allergy to broccoli
- Participant unable to understand the study information
- Participation in other clinical trial which may affect the outcome of the present study
- Any other physical or psychiatric condition or treatment that in the judgment of the investigator makes it difficult to participate in the study.

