## **6. STATISTICS AND DATA HANDLING**

### **6.1 Statistics**

The primary effect variable is venous fasting blood glucose. Participants will be analysed using intraindividual one-tailed comparisons before and after treatment and compared between the placebo and BSE arms using Student's t-test. The study hypothesis is that participants taking BSE for 12 weeks will have at least 0.3 mM lower fasting blood glucose on average than participants taking placebo. The intra-individual standard deviation of fasting blood glucose is 0.63 mM, based on analyses in our longitudinal cohorts of subjects with impaired fasting blood glucose. We therefore need 37 participants in each randomization group to detect a difference of 0.3 mM in fasting blood glucose between the groups at 80% power at  $p < 0.05$ . We aim to recruit 50 participants in each group to cover for potential dropouts.

We will also make a subgroup analysis of participants with fasting triglycerides above median. This is based on our previous study on BSE (Axelsson et al.) showing that BSE is particularly effective in individuals with increased triglyceride levels. It is known that increased triglycerides are more common in subjects with elevated fatty liver content (Gastaldelli et al., 2009) and we therefore want to investigate whether this subgroup of the population would benefit more from BSE.

Both Intention-to treat (ITT) and per protocol (PP) analysis of the outcome variables will be performed and ITT will be used as a basis for the conclusions. Missing values will be replaced by the latest value available. Participants with poor compliance (see 5.4) will however not be included in any analyses.

The secondary study variables, HbA1c, fatty liver index, fasting lipids, free fatty acids, insulin, HOMA-IR and weight, will be analysed using intraindividual comparisons between visit 2 and 3.

We will later analyse stool samples to investigate changes in abundance of bacterial strains between the BSE and placebo groups.

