## **7. SAFETY**

### **7.1 Safety of BSE**

Cruciferous vegetables, including broccoli sprouts, are generally regarded as safe and are regular dietary components in many regions of the world.

Shapiro et al. 2006 conducted a double-blind, placebo controlled, randomized study of BSE in healthy individuals to determine the safety and tolerance of repeated oral administration. Twelve healthy human volunteers received doses of BSE every 8 hours for 7 days (total 21 doses) while undergoing clinical evaluation and a battery of laboratory tests. Subjects received BSE corresponding to 75 – 300  $\mu$ mol sulforaphane daily. No clinical adverse events were reported. Two of 12 individuals (both receiving BSE) showed an increase in plasma ALT exceeding the upper limit of normal. Notably, ALT levels rose for all subjects during the course of the study including placebo-treated subjects. Plasma AST levels rose above normal on day 19 for 2 of 12 subjects. Monitoring of TSH levels demonstrated that in 3 of 12 subjects (2 active treatments, 1 placebo), TSH levels exceeded the upper limit of normal during or after the dosing period. TSH increases were not associated with any clinical symptoms or abnormalities of T3 or T4. Evaluation by 2 independent endocrinologists determined that the changes in TSH were mild and reversible and did not pose an obstacle to further studies with BSE administration. No other significant laboratory abnormalities occurred. Thus, this safety study in healthy volunteers revealed no evidence of systematic, clinically significant adverse effects that could be attributed to the administration of BSE.

Kensler et al. 2005 conducted a human study enrolling 200 subjects. Healthy subjects were randomized to receive BSE containing 400 micromol sulforaphane (twice the dose we will use) or placebo nightly for 2 weeks. Subjects were followed clinically for compliance and adverse events. The BSE was well tolerated. 199 subjects completed all doses in the study without reporting any adverse events.

In a recent study of men with recurrent Prostate Cancer Alumkal et al. 2015 found that treatment with 200 micromol (the same dose that we will use) of sulforaphane per day for 20 weeks produced no major side effects.

The main potential AEs as reported previously might be expected to include gastrointestinal symptoms such as indigestion, belching, or loose stools.

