## **8. ETHICAL ASPECTS**

### **8.1 Risks - benefit**

The study will be done in accordance with applicable laws and regulation and the principles of GCP and the Helsinki Declaration.

The benefits from participating exceed the risk in our opinion. Broccoli sprouts are used as a food supplement all over the world. BSE has been given in >30 clinical studies ([www.clinicaltrials.gov](http://www.clinicaltrials.gov)). These studies have used BSE with up to 420  $\mu$ mole sulforaphane (we will use 150  $\mu$ mole) between 2 and 20 weeks (we will do 12 weeks treatment) and no serious adverse events or severe perturbations of routine blood analytes have been reported.

The only invasive procedures are the capillary and venous cannulations, which may give local pain.

There are several benefits for the participants, as they get a better characterization of their blood glucose levels and since we examine a number of blood analytes such as creatinine, liver status and lipid levels. We will follow up any abnormal values through referrals, including any suspected diabetes mellitus that is previously unknown.

If the treatment is effective it would provide a new means to lower blood glucose in the population that can serve as a “functional food”.

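### Randomised participants who are diagnosed with diabetes or start anti-diabetic medication must be withdrawn, and no visit 3 glucose is provided for, so the ITT analysis scores them as unchanged

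*Protocol*

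**What the plan says.** Under Criteria for withdrawal (section 3.2) the rule is mandatory: "The participant will be withdrawn should they develop any condition or begin taking any compound that is part of the exclusion criteria". The exclusion list in the same section contains "Diagnosed with diabetes mellitus according to the WHO criteria" and, as a separate item, anti-diabetic medication. It also contains "Gastrointestinal ailments which may interfere with the ability to adequately absorb sulforaphane".

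The withdrawal section is about leaving the study. Its first bullet reads "The participant can withdraw from the study at any time without further motivation". Its closing sentence gives the only stated consequences: "All participants that are withdrawn will continue their regular medication and their ordinary physician will be notified as appropriate". It mentions no early-termination visit and no later blood sample.

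Venous fasting glucose, the primary variable, is taken at screening, visit 2 and visit 3 only (section 4.3). Section 6.1 says "ITT will be used as a basis for the conclusions", replaces a missing value by the latest one available, and removes participants with poor compliance from every analysis. Section 8.1 promises referral of abnormal values, "including any suspected diabetes mellitus that is previously unknown".

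**The concern.** At entry these exclusions define the population. After randomisation, a diabetes diagnosis or a glucose-lowering prescription in a trial of impaired fasting glucose is a poor result on the quantity being measured. Ending participation at that point, with no outcome sample foreseen, makes missingness depend on the outcome and, if BSE works, on the arm.

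The carry-forward rule then completes the record with the visit 2 value, so a person whose glucose rose enough to be diagnosed enters the ITT comparison with a change of zero. A later analysis plan can choose another way to fill the gap, but it cannot create a measurement that was never scheduled. That makes this a matter for the protocol.

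**Working it through.** **No figure in the plan to reproduce.** The documents give no rate of diabetes diagnosis, new medication or withdrawal. What follows shows scale under stated assumptions.

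**Inputs from section 6.1:** difference 0.3 mM, SD 0.63 mM, one-sided test at 0.05, 50 per arm.

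**Assumptions:**
- Visit 2 glucose *b* is uniform on 6.1-6.9 mM, the entry range.
- Change *c* is normal with SD *s* = 0.63 and mean *m* = 0 on placebo, -0.30 on BSE (0.63 is read as the SD of change).
- A share *q* of those whose follow-up glucose would be 7.0 mM or more is diagnosed or treated and withdrawn before visit 3.
- The visit 2 value is carried forward, so their change is 0.

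**Step 1. Probability of reaching 7.0 mM.** Average 1 - Φ((7 - *b* - *m*)/*s*) over *b*: placebo 0.229, BSE 0.117, ratio 0.229/0.117 = 1.96. The share lost is *q* times these.

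**Step 2. Change erased by setting these people to zero.** Average *m*[1 - Φ(*u*)] + *s*φ(*u*), with *u* = (7 - *b* - *m*)/*s*, over *b*: placebo 0.179 mM, BSE 0.081 mM, gap 0.098 mM.

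**Step 3. Expected ITT difference** = -0.30 + *q* × 0.098.

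**Step 4. Power** = Φ(|difference|/SE - 1.645), with SE = 0.63 × √(2/50) = 0.126 mM, SD held at 0.63.

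| *q* | Lost, BSE | Lost, placebo | Difference (mM) | Power |
|---|---|---|---|---|
| 0 | 0 | 0 | -0.30 | 0.77 |
| 10% | 1.2% | 2.3% | -0.29 | 0.74 |
| 25% | 2.9% | 5.7% | -0.28 | 0.71 |
| 50% | 5.8% | 11.4% | -0.25 | 0.64 |
| 100% | 11.7% | 22.9% | -0.20 | 0.48 |

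At *q* = 25% that is 50 × 0.057 = 2.9 people on placebo and 50 × 0.029 = 1.5 on BSE. The shift is 0.25 × 0.098 = 0.024 mM, or 0.024/0.126 = 0.19 standard errors. The 100% row is only a bound.

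The starting power of 0.77 is below 0.80 because the two-sample formula with these inputs needs 55 per group; that is a separate matter.

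**Step 5. If these people were dropped instead of carried forward,** the differences for *q* = 10%, 25% and 50% are -0.295, -0.284 and -0.260. The result hardly depends on how the gap is handled.

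**Step 6. Direction.** Loss unrelated to glucose course can also move the estimate. With 10% lost on BSE, none on placebo and a placebo fall of 0.2 mM: 0.9 × (-0.5) - (-0.2) = -0.25, and with no true effect 0.9 × (-0.2) - (-0.2) = +0.02, against BSE. With the 10% lost on placebo only: -0.5 - 0.9 × (-0.2) = -0.32. The pull is therefore mainly, not always, toward zero.

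**Step 7. Would a retained visit 3 value be used?** Section 5.4 requires more than 75% of doses overall and more than 80% in the last month. Someone followed for 12 weeks who stopped product at week 9 has taken at most 9/12 = 75% and fails; so does anyone who misses more than 0.2 × 28 = 5.6 days of the last four weeks. Section 6.1 then removes that person from all analyses. Amending the withdrawal section alone would collect values that section 6.1 discards.

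**The case against.** The strongest reply is that the trigger will seldom fire. No study glucose is taken between visits 2 and 3; the only planned contact is a telephone call (section 3.6). Section 3.3 notes that diabetes has to be confirmed by a second glucose analysis. A high value first seen at visit 3 is already in the data. The trigger therefore needs a diagnosis or prescription outside the study within about 12 to 15 weeks. This stands, and it is why the larger shares in the table are unlikely.

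A reader might infer four stronger things that the documents do not support:

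- **That the protocol forbids sampling after withdrawal.** It is silent. The defect is that nothing provides for the sample.
- **That the ordinary side effects of BSE force withdrawal.** Section 7.1 expects "gastrointestinal symptoms such as indigestion, belching, or loose stools", but the exclusion covers only ailments that may impair absorption of sulforaphane. Loose stools might qualify; belching alone would not. This is a secondary route of unknown size.
- **That referral on visit 2 bloods biases the comparison.** HbA1c is first drawn at visit 2 and does not gate randomisation, so referral and withdrawal could follow. But that blood precedes treatment, so such cases are balanced between arms in expectation. They cost outcomes without favouring an arm. Differential loss needs a diagnosis arising after randomisation.
- **That a false positive result is likely.** In the glucose-driven scenarios the true difference shrinks.

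**Conclusion.** The point holds in a limited form. The withdrawal rule ends participation on events that belong to the outcome, provides no visit 3 measurement afterwards, and leaves an ITT analysis to score a participant who progressed as unchanged. That fits poorly with drawing conclusions from ITT.

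The likely size is modest: about 0.01 to 0.05 mM off a difference of 0.30 mM, with power falling from 0.77 to between 0.74 and 0.64, if 10% to 50% of those reaching 7.0 mM are withdrawn before visit 3. This rests on the assumed baseline range, SD of change and shares. The case for acting is the low cost and the fact that uncollected values cannot be recovered, more than the expected size of the bias. Whether a participant should stop product in these circumstances is a clinical matter and is not judged here.

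**What to change.** Two linked changes are needed.

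1. **Section 3.2, Criteria for withdrawal.** Leave the conditions for stopping product as they are. Add that a participant who stops product under these criteria remains in follow-up unless consent is withdrawn, and attends visit 3 as planned for fasting glucose and the secondary bloods. Record the start date of any anti-diabetic medication.
2. **Section 6.1.** Restrict the poor-compliance exclusion to the per-protocol analysis, so that these visit 3 values enter the ITT analysis in the randomised arm. Without this, the first change achieves little.

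The cost is a short amendment. Visit 3 is already planned for every participant, so few if any extra procedures arise. The downside is small: some values measured off product or after new medication enter the ITT estimate, and with start dates recorded their influence can be examined.

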### 3.3 Screening visit

Participants who have booked a time for a screening visit are instructed (by a confirmation email) not to conduct intense physical activity or drink alcohol 24 h before the visit. They should be fasting since midnight. Nicotine users should not have used nicotine the same day.

At the screening visit the study personnel first informs the participants (in group) on what it means to participate in the study (this has also been described in the initial participant information sent by post). The participants who are interested in taking part then meet a member of the personnel on their own where they can ask questions and study criteria are being checked. Participants who sign a written informed consent will then undergo capillary fasting blood glucose measurement.

The capillary fasting blood glucose is analysed by a glucometer on-site. If the capillary fasting blood glucose is 6.0-6.9 mmol/l we proceed with venous blood sampling to analyse the study criteria, as well as weight and length measurements. If it is obvious that the participant will not fulfil the study criteria (based on capillary blood glucose measurement or the study criteria that we can assess without blood analyses) we do not proceed with venous blood sampling.

The participant gets a screening number (S1, S2, etc.). The code list for screening number and screening ID is kept with the Investigator. Those who come to a screening visit but are not eligible to participate will continue to be managed by their regular physician. If blood glucose is 7.0 mM or above (which means risk for diabetes diagnosis, which has to be confirmed by a second glucose analysis), the individual will be referred to primary healthcare to assess whether they have overt diabetes.

The following will be done at the screening visit:

- The participant will receive information on the study in group
- Each participant meets a member of the study staff on their own and can ask questions
- Written informed consent is signed if the participant wants to take part
- ID is checked
- Information on current use of pharmaceutical drugs is collected
- Inclusion and exclusion criteria are checked
- The participant gets a screening number.
- Capillary fasting blood glucose is analysed on-site.

If capillary fasting blood glucose is 6.0-7.9 mM we proceed with the following:

- Length, weight, and waist-hip circumference are measured.
- Venous fasting blood samples are drawn for analysis of glucose, creatinine, ASAT, ALAT, GT, ALP, bilirubin, PK, thrombocytes. Total blood volume is estimated to 25 mL.
- If venous fasting blood glucose is above or equal to 6.1 mmol/l and below 7.0 mmol/l, the participant is scheduled for visit 2, which will be 1-14 days after

the screening visit.

- They receive a tube for stool sampling and are instructed how to sample.

### 3.4 Visit 2

Participants who are eligible to participate will be scheduled for a second visit 1-14 days after their first visit. If the venous analyses from the screening visit of creatinine, ASAT, ALAT, GT, ALP, bilirubin, PK, thrombocytes, show clinically relevant abnormalities that upon decision by PI precludes participation, that the subject's visit 2 will be cancelled.

The participants are recommended not to conduct intense physical activity or drink alcohol 24 h before the visit. They should be fasting since midnight. Nicotine users should not have used nicotine the same day.

The following will be done at visit 2:

- ID is checked
- Information on current use of pharmaceutical drugs is collected
- Venous fasting blood samples are drawn for analysis of fasting glucose, HbA1c, insulin, c-peptide, Hb, GT, lipid levels (HDL, LDL, total cholesterol, triglycerides), TSH and free fatty acids. Total blood volume is estimated to 25 mL.

If venous fasting blood glucose is 6.1-6.9 mM the individual can be included in the study and we proceed with the following:

- For women of fertile age we make a pregnancy test and proceed with the remaining points only if that is negative.
- The participant receives a study ID, using consecutive numbers and are randomized to receive BSE or placebo (see point 5.3 Randomization)
- Length, weight, and waist-hip circumference are measured.
- Participants complete a questionnaire on dietary habits, physical activity, smoking and alcohol habits.
- Participants leave their stool sample
- A note is made in the medical record about the visit.
- Study subjects receive their study medication (BSE or placebo) to bring home
- They receive a tube for stool sample to be sampled before visit 3
- Scheduled for visit 3. Visit 3 should be scheduled on the same weekday as visit 2, 12 (ideally) or 13 weeks later. If that is not possible, e.g. because of public holidays or unavailability of the participant to come on an assigned day, visit 3 will be scheduled as soon as possible 12 weeks after visit 2. Latest possible date for visit 3 is 14-15 weeks after visit 2. If that is not possible to manage for the participant, he or she have to be excluded. The participant is instructed to contact us as soon as possible if he or she needs to change date for visit 3.

### **3.5 Inclusion**

If the participant fulfil all study criteria they will be formally included. Included participant receive a study ID (1, 2, 3, etc.). The study ID will be different from the screening number (S1, S2, S3, etc.). The code list for study ID and personal ID is kept with the Investigator. Included participants will receive a card with information about the study and contact details to the study team. The card holds instructions to caregivers to contact the Investigator should the participant's medication be changed during the course of the study. The participant continues taking all their regular treatment during the study. Only coded data, based on the study number, will be used for analyses.

### **3.6 Between visit 2 and 3**

Participants are instructed to take their BSE/placebo daily in the morning starting 12 weeks before visit 3. They have a paper attached on the box with their medication/placebo where they tick each day they have taken a dose. They will receive a slight surplus, in case they for some reason have to postpone visit 3. The reason is that we want to avoid gaps between the last intake and visit 3. If a participant or the study team with short notice have to cancel visit 3, e.g. due to illness, and the participant runs out of study medication we must have a buffer so that the treatment can continue daily until visit 3. The total treatment time can under no circumstances be more than 15 weeks, and if visit 3 has to be postponed beyond that limit the participant will be excluded. Any remaining doses should be brought back to the study team at visit 3.

The study team will contact the participants by phone 2-4 weeks after the initiation of the treatment to ask whether they experience any side effect and to check compliance. Moreover, information on changes in use of pharmaceutical drugs is collected. Reasonable efforts should be undertaken to get into contact with the participants by calling back if no reply, leaving messages and as a second option sending emails. Participants are also instructed to contact us in case they have any suspected side effects of the treatment.

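### Sections 3.4 and 3.6 exclude already randomised participants when visit 3 is late, so their only outcome reading is lost or carried forward, and the two time limits start from different points

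*Protocol*

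**What the plan says.** **Order of events (3.4).** At visit 2 participants receive a study ID and "are randomized to receive BSE or placebo". They take the product home, and visit 3 is booked at the same visit.

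**Limit counted from visit 2 (3.4).** The normal booking is 12 or 13 weeks: "Visit 3 should be scheduled on the same weekday as visit 2, 12 (ideally) or 13 weeks later". Public holidays and participant unavailability are given as reasons for a later date. Then: "Latest possible date for visit 3 is 14-15 weeks after visit 2". The consequence follows directly: "If that is not possible to manage for the participant, he or she have to be excluded".

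**Limit counted from first dose (3.6).** The first dose is timed by counting 12 weeks back from visit 3, so it can fall after visit 2. Treatment is capped at 15 weeks, and "if visit 3 has to be postponed beyond that limit the participant will be excluded". The situation foreseen is a late cancellation: "If a participant or the study team with short notice have to cancel visit 3, e.g. due to illness".

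**Analysis (6.1).** ITT and per-protocol analyses are both planned, and "ITT will be used as a basis for the conclusions". Missing values are filled with the last one recorded. Poor compliers are the only group that 6.1 removes from every analysis.

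**Outcome (3.7, 4.3).** Venous fasting glucose is measured at screening, visit 2 and visit 3. Only the last of these comes after treatment has begun.

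**The concern.** An exclusion rule that acts after randomisation can undo what randomisation provides. Here the trigger is only the date of the outcome visit. Someone who took every dose is caught, so this is a different rule from the poor-compliance one.

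The protocol's own example of a short-notice cancellation is illness. Illness need not be unrelated to arm or to glucose, although other listed reasons (holidays, unavailability, cancellation by the study team) have no evident link to either.

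With one reading after treatment has begun, a participant who is excluded before visit 3 has no outcome at all. What happens to that person in the primary comparison then depends on an analysis convention, and the protocol does not say which one applies. Staff must also decide who is late from two limits that start at different points, one of them written as a range.

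**Working it through.** The protocol gives no rate of late visits and no figure for their effect, so there is no planned number to reproduce. The check compares the two limits and then follows an excluded participant through 6.1.

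**1. The two limits on one scale**

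Let P be the booked week of visit 3, counted from visit 2. By 3.6 the first dose falls at week P − 12. The 15-week treatment cap is then reached at week (P − 12) + 15 = P + 3 after visit 2. The limit in 3.4 stays at week 14-15.

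| Booked week P | First dose (week) | Treatment cap reached (week after visit 2) | Limit in 3.4 (week after visit 2) | Gap (weeks) |
|---|---|---|---|---|
| 12 | 0 | 15 | 14-15 | 0 to 1 |
| 13 | 1 | 16 | 14-15 | 1 to 2 |
| 14 | 2 | 17 | 14-15 | 2 to 3 |
| 15 | 3 | 18 | 14-15 | 3 to 4 |

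The limits coincide only if dosing starts on the day of visit 2 and the range is read as 15 weeks. On the expressly permitted 13-week booking, a visit moved to week 16 is 16 weeks after visit 2, beyond the limit in 3.4. It is 16 − 1 = 15 weeks into treatment, so the cap in 3.6 is not exceeded. Even on the ideal 12-week booking, a visit between weeks 14 and 15 is in or out depending on which end of the range is used.

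**2. If exclusion means removal from the ITT set**

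If a share p of one arm is removed and their mean change differs by d from those kept, the arm mean shifts by p × d. Both inputs are assumed, because the protocol gives neither:

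- p = 2%, d = 0.3 mM: 0.02 × 0.3 = 0.006 mM
- p = 5%, d = 0.3 to 0.6 mM: 0.015 to 0.03 mM
- p = 10%, d = 0.6 mM: 0.10 × 0.6 = 0.06 mM

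Against the 0.3 mM target this is 0.006/0.3 = 2% to 0.06/0.3 = 20%. If removal were unrelated to outcome, d would be 0 and only numbers would be lost.

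**3. If the participant stays in ITT by carry-forward**

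The last glucose before a missing visit 3 is the visit 2 value. With visit 2 as baseline, the change is visit 2 − visit 2 = 0. If a share f of both arms is handled this way, and the true effect is the same in those affected, the expected difference is 0.3 × (1 − f):

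- f = 2%: 0.3 × 0.98 = 0.294 mM
- f = 5%: 0.3 × 0.95 = 0.285 mM
- f = 10%: 0.3 × 0.90 = 0.27 mM

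Either way, the fasting glucose that these participants could have provided does not enter the analysis.

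**The case against.** **Loss from ITT is an inference.** A reader might conclude that late attenders are dropped from the ITT set. The documents do not support that as a statement of fact. Where the protocol means removal from all analyses, it says so in 6.1, and only for poor compliance. The carry-forward rule could keep late attenders in. Assigning such cases to analysis sets is also commonly left to a statistical analysis plan, which is not at hand. This stands, and the point is limited accordingly. It does not dispose of the conduct rule, because no analysis plan can recover a sample that was never taken.

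**The limits are both upper caps.** A reader might infer an outright contradiction, with 3.6 retaining a person whom 3.4 excludes. The text does not go that far. Section 3.6 says who is excluded and does not say that everyone below the cap is kept, so both limits can be applied together. What remains is that they start at different points and that 14-15 weeks gives no single cut-off.

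**The numbers affected may be small.** The ideal schedule leaves up to three weeks of slack, surplus product is supplied, and several listed reasons for delay are neutral. This is fair. No claim about the actual frequency or direction of bias can be made. The recruitment margin for dropouts replaces lost numbers, but it does not restore comparability if the losses are selective.

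**Late samples may be off product.** Section 3.6 deliberately tries to avoid a gap between last intake and visit 3. That is a real cost of taking the sample late, and a reason for a per-protocol analysis without such visits. It is not a reason to have no reading.

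**Conclusion.** The point holds in a limited form. Sections 3.4 and 3.6 exclude randomised participants for a late visit 3 regardless of adherence and make no provision for their outcome sample. Under one reading the ITT set is no longer the randomised set. Under the other, a change of zero stands in for the outcome.

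The size is unknown. The illustrations run from 0.006 to 0.06 mM for a shift in one arm's mean, and from 0.294 down to 0.27 mM for a diluted 0.3 mM effect. They rest on assumed shares of 2-10% and, for the shift, an assumed difference of 0.3-0.6 mM. They are not estimates for this trial.

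The two time limits need reconciling. Which of them is right is not judged here. The change is worth making because it is cheap and protects the analysis that carries the conclusions; the point does not by itself invalidate the design.

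**What to change.** - **3.4 and 3.6:** replace exclusion by a statement that visit 3 and its fasting sample are still obtained as soon as possible, that the actual visit and last-dose dates are recorded, and that the participant stays in the ITT analysis with the observed value.
- **Treatment-time limit:** leave unchanged.
- **Visit 3 window:** reconcile 3.4 and 3.6 into one window, with one starting point and one cut-off.
- **5.4 and 6.1:** add that visits outside the window are left out of the per-protocol set only. At present 5.4 defines that set by compliance alone, so this is a new rule.
- **Compliance count:** state that days after product has properly ended do not count as missed doses. Otherwise, if the last month is read as the 28 days before visit 3, a 7-day gap gives 21/28 = 75%. That fails the 80% criterion, and 6.1 would remove the person from all analyses by another route.

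The cost is protocol wording, with no added participants or scheduled visits. The downside is that a few samples will be late or taken after product has ended, which tends to dilute any effect in ITT. The per-protocol analysis already planned addresses this.
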